## **Executive Summary**

*Background:* A comprehensive evaluation of the IMB Mental Health program's innovative model of integrated mental health care at health centers (MESH MH) is needed to provide feedback for ongoing implementation and growth of the program. Evidence of increased uptake and acceptable quality of care by health center nurses, as well as improved patient clinical outcomes, must be documented before scale up of the MESH MH program to a national level could be considered.

*Objectives/Methods:* A mixed-methods outcomes evaluation with a pre- and post-test design will be performed at four purposively selected health facilities participating in the MESH MH program. Qualitative and quantitative outcome evaluations will be conducted to determine whether patients who receive mental health care at supported health centers (HCs) experience clinical and functional improvement and to explore the perspectives and experiences of health workers and patients who receive care through this program. As an adjunct to these evaluations, a process evaluation will be conducted using service utilization data to assess changes in uptake of mental health services at participating health facilities within the district, and use MESH supervision checklists to determine whether participating HC nurses adequately provide basic quality mental health care.

*Population:* Routine program monitoring data will be collected from the registries for all patients attending mental health services at district health centers and outpatient mental health clinic. All adults arriving for a mental health visit at selected health centers who are diagnosed with a neuropsychiatric disorder will be asked to participate in the quantitative portion of the evaluation. Patients who need to be transferred to the district hospital for an acute medical or psychiatric emergency and patients with a primary alcohol or substance use disorder will be excluded from the evaluation. Approximately eight nurses and fifty "information rich" patient and family participants will be selected purposively for the qualitative evaluation.

*Outcome measures:* Patients' mental health status, daily functioning, and economic status will be measured at baseline, eight weeks and four months using three clinician administered rating scales: the General Health Questionnaire (GHQ-12), the World Health Organization Disability Assessment Scale (WHO-DAS 2.0 Brief), and a brief economic questionnaire. Qualitative semi-structured interviews will be used to understand the meaning that users, families and providers ascribe to any statistical associations found in the quantitative analyses, and to provide rich descriptions of experiences and perceptions of the program.

## Background and Rationale

Neuropsychiatric disorders account for about one quarter of the global burden of disability, yet rarely receive priority among the many health conditions competing for political will and allocation of funds. In most countries, the extreme shortage of mental health specialists has led to a gap of up to 90% between treatment need and available mental health services, despite the known efficacy of both pharmacological and psychosocial interventions for treating major mental disorders. Innovative solutions that integrate mental health care into routine health platforms and optimize health worker interventions through ‘task-shifting’ – delegating tasks and responsibilities from more specialized to less specialized health workers – could contribute to effective treatment implementation and alleviating the burden of neuropsychiatric disorders in low income settings.

The Republic of Rwanda’s National Strategic Plan for Mental Health (revised 2011) calls to reduce the treatment gap in Rwanda by locating mental health services within public district health systems. Since 2005, the Ministry of Health (MOH)’s mental health decentralization efforts have succeeded in placing at least one psychiatric nurse and psychologist at each of forty one district hospitals in Rwanda, although the ratio of public mental health workers to population within each district remains low. To address this shortage, the Strategic Plan also calls for the integration of mental health into primary care health services offered at health centers. Evidence suggests that primary care workers who receive adequate training and supervision can successfully recognize and treat a range of mental disorders using evidence based practices. Yet few models exist for the effective implementation and delivery of quality mental health services within primary care settings in resource limited areas.

Integration of mental health care into primary care is most likely to work well using existing systems of management and supervision as a starting point. Partners In Health (PIH), a non-profit organization working in twelve countries, has been supporting the public health delivery system in three rural districts of Rwanda since 2005. In collaboration with the MOH, PIH/IMB (Inshuti Mu Buzima) has implemented the MESH program (Mentoring and Enhanced Supervision at Health Centers) to improve the quality of care provided by nurses at first level health facilities in IMB supported districts of Rwanda. MESH supports health center nurse implementation of key child and adult clinical protocols by incorporating decentralized didactic training with ongoing clinical mentorship and quality improvement activities at health centers. The model follows closely with World Health Organization (WHO) clinical mentoring guidelines developed for effective task shifting of HIV care. Initial results from the MESH program demonstrate significant improvement in a number of quality-of-care indicators after mentoring. The MESH program is currently being brought to scale nationally for HIV care in all forty one districts in Rwanda, with preliminary plans in place for further future scale up in other clinical domains.

### *MESH Mental Health Program*

MESH provided a robust platform through which to translate the national policy of decentralized mental health care into action and create a scalable model for primary care mental health services in rural Rwanda. In August 2012, IMB partnered with the MOH in Burera district, northern Rwanda, to integrate mental health care into health center primary care services using the MESH platform. Burera district is served by Butaro hospital, a 150-bed public hospital with approximately thirty five general nurses, thirteen full time general practitioners, four psychiatric nurses and one psychologist. The hospital is the primary referral center for seventeen health centers, and serves an overall population of approximately 340,000 people.

Three health centers in Burera district were initially chosen to pilot the MESH mental health (MESH MH) program. Four major neuropsychiatric disorders were chosen for clinical focus based on needs perceived by district mental health staff and health center directors, informal observation of diagnoses as listed in health center registers, and evidence of disease burden and treatment effectiveness as defined by the World Health Organization (WHO): schizophrenia, bipolar disorder, major depressive disorder, and epilepsy. After an intensive, forty-hour training designed to teach primary care nurses how to identify and manage these four disorders, a program of regular supervision by a trained Rwandan mental health nurse was initiated. Health center supervisory visits included clinical observation, individual case review, documentation review, and brief didactic sessions. A mental health supervision checklist was adapted from other MESH areas of clinical focus, to assist with clinical mentoring and to ensure standardization of activities across clinical domains. The mentor nurse used the case observation checklist to ensure that health center nurses were performing key elements of basic psychiatric evaluations, accurately diagnosing patients and offering appropriate treatment and support based on diagnosis. The successful completion of checklist items during mental health clinical evaluations was used to define basic quality of care provided by health center nurses. During each supervision session, the nurse-mentor also discussed systems based performance issues and “quality gaps” with the health center director and the health center nurses, and formulated specific plans to improve patient care, referral pathways, coordination between services, and other systems level issues.

### *Program Research Evaluation*

Preliminary informal reports from Butaro district hospital staff, participating health center nurses and patients indicate that the MESH MH program has been received well at the three pilot health centers. In August 2013, the program was implemented at three additional health centers in Burera district, and in FY15 through FY17, the program will be implemented at all remaining health centers in the district. Although the program has an initial high level of acceptability and feasibility within the district health services, there is an urgent need for a comprehensive evaluation of MESH MH programming within the district system of care. Rigorous evaluation of MESH MH will provide valuable feedback for ongoing implementation and growth of the program. Additionally, evidence of increased service uptake and acceptable quality of care by

health center nurses, as well as improved patient clinical outcomes, must also be documented before scale up of the MESH MH program to a national level could be considered.

### **Study goals and objectives**

Aim 1: Assess changes in uptake of mental health care by assessing the quantity and quality of mental health diagnoses at Burera district health centers in relation to the implementation of the MESH MH program.

Aim 2: Assess whether participating non-specialist health center nurses offer basic quality mental health care as specified in MESH MH program objectives.

Aim 3: Assess whether patients who receive mental health care at select health centers experience clinical and functional improvement, including economic status

Aim 4: Explore the perspectives and experiences of health center nurses, families and patients who receive care at select health centers where the MESH MH program has been implemented

### **Study Design**

A mixed-methods outcomes evaluation with a pre- and post-test design will be performed. This design will allow for multiple data sources to be used to evaluate the MESH mental health program in its context. A simultaneous qualitative and quantitative outcome evaluation will be conducted to determine if the MESH MH program implementation is associated with clinical improvement for patients. A process evaluation will use service utilization data and supervision checklists (quality) to determine whether the MESH program has been successfully implemented at participating health centers and if the intended services are being provided. The process evaluation will serve as an adjunct to the outcomes evaluation in order to associate outcomes with rigor of implementation in program activities.

### **Methodology**

#### ***Process Evaluation: routine quantitative program data***

Routine program monitoring data will be collected for three months prior to and six months following the implementation of the MESH program, to assess whether increases in mental health diagnoses occur in relation to implementation of MESH. An increase in the number of visits following MESH implementation will be interpreted as an increase in uptake of mental health services.

All health centers participating in the MESH program in Burera district will be surveyed. At each health center, the total number of patients with a mental disorder seen at each health center per month, the number of new patients diagnosed with a mental disorder each month, and the number of patients who receive any follow-up over the course of six months will be recorded. In addition, demographics (including age, gender and village), and the diagnosis and treatment as

recorded in the health center register, will be documented for each patient. These routine data will also be collected from the Butaro district hospital outpatient mental health clinic to assess district wide service use.

Patient diagnoses and visit data are currently routinely recorded in the daily register by clinicians at all health facilities in the district. Each month, a research data officer will travel to participating health facilities and record these process indicators. The data will be entered into an electronic patient database currently in use by the IMB MH team for tracking routine process indicators. A subset of these data will be routinely reviewed for accuracy and completeness by the PI by comparing them with the paper registers at the participating facilities. The database is held on a team computer which is password protected and kept by the IMB MH team at Butaro hospital.

*Data analysis:* We will compare the number of new patients diagnosed with a mental disorder, the number of new mental health diagnoses, the number of mental health follow-up visits, and % of patients with specific diagnoses pre- and post- MESH MH program implementation. We will also compare new and follow up data from health centers with routine data from the district mental health clinic. We hypothesize that we will observe an increase in the number of mental health diagnoses and follow-up visits at health centers post-MESH implementation, representing an increase in uptake of mental health services and recognition of mental health morbidity among providers. We further hypothesize that MESH training will lead to improvements in the number of individuals with specific mental health diagnoses post-MESH.

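### Uptake is judged on numbers from three months before and six months after implementation with no time denominator, and season is not controlled within a centre

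*Protocol*

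**What the plan says.** All of this is in the Protocol, mainly under Process Evaluation: routine quantitative program data.

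- **Windows:** "Routine program monitoring data will be collected for three months prior to and six months following the implementation of the MESH program".
- **Interpretation rule:** "An increase in the number of visits following MESH implementation will be interpreted as an increase in uptake of mental health services".
- **Quantities compared:** "We will compare the number of new patients diagnosed with a mental disorder, the number of new mental health diagnoses", together with "the number of mental health follow-up visits, and % of patients with specific diagnoses pre- and post- MESH MH program implementation".
- **Hypothesis:** "We hypothesize that we will observe an increase in the number of mental health diagnoses and follow-up visits at health centers post-MESH implementation".
- **Recording units:** two indicators are monthly, namely "the total number of patients with a mental disorder seen at each health center per month" and "the number of new patients diagnosed with a mental disorder each month". A third counts patients with any follow-up within a six-month span.
- **Concurrent data:** the same routine data come from the district hospital's outpatient mental health clinic, and health-centre figures are to be compared with them.
- **Start dates:** the section on the MESH Mental Health Program dates the partnership behind the three pilot centres to August 2012. For the second wave, "In August 2013, the program was implemented at three additional health centers in Burera district". The remaining centres follow in FY15 to FY17, with no months given.

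**The concern.** The windows differ in length by a factor of two, while the comparison, the hypothesis and the interpretation rule are all expressed as numbers. Nothing in the section says that the numbers are per month or that equal windows are used. A reader applying the rule literally could report increased uptake where use had not changed.

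A second difficulty remains if monthly rates are used. Three months before and six months after a start date make nine consecutive months, so a centre never contributes the same calendar month to both periods.

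The stakes are moderate. Uptake is Aim 1. The Executive Summary and Program Research Evaluation make evidence of increased uptake one of the conditions for considering national scale-up. The Limitations section relies on the process evaluation to support attributing clinical change to the programme in a study without a control group. The patient-level primary outcomes are not affected.

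**Working it through.** The protocol gives no sample size, alpha, test or expected count for the uptake comparison, so there is no stated figure to reproduce.

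**Inputs**
- From the protocol: 3 months before, 6 months after.
- Assumed, because no figure is given: an expected count of L per month, from 2 to 50, unchanged by the programme and Poisson distributed; seasonal amplitude of 10% to 30% around the annual mean.

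**1. Period totals under no change.** Expected totals are 3L and 6L, so the ratio is 6L/3L = 2.0 for any L. If true monthly use becomes f times its former level, the ratio is 6fL/3L = 2f. This exceeds 1 whenever f > 0.5, so a fall of just under half still appears as an increase.

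**2. How often no change would look like an increase.** The third column gives the chance that the later total is larger. The fourth is an illustrative test of equal totals (exact conditional binomial, p = 0.5, upper tail 0.025). The fifth is the same test allowing for observation time (p = 6/9).

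| L per month | Expected totals | P(later total larger) | Test ignoring time finds increase | Test allowing for time finds increase |
|---|---|---|---|---|
| 2 | 6 and 12 | 0.905 | 0.22 | 0.012 |
| 5 | 15 and 30 | 0.986 | 0.56 | 0.016 |
| 10 | 30 and 60 | 0.999 | 0.87 | 0.019 |
| 20 | 60 and 120 | about 1.00 | 0.99 | 0.021 |
| 50 | 150 and 300 | about 1.00 | 1.00 | 0.022 |

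**3. Monthly averages under no change.** (6L/6)/(3L/3) = 1.0. The doubling disappears.

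**4. Patients with any follow-up.** This indicator cannot be repaired by dividing by months. Suppose, for illustration, that each patient in a fixed group has the same independent chance q of a follow-up in each month. The proportion with at least one is 1 − (1 − q)^3 over three months and 1 − (1 − q)^6 over six. Their ratio is 1 + (1 − q)^3, which lies between 1 and 2 with no change in care. Dividing each by its months gives (1 + (1 − q)^3)/2, which is below 1. The windows themselves must be equal.

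**5. Season, after moving to monthly rates.** For a start in August, the months before are May to July and those after are August to January: no overlap. For a seasonal curve 1 + a·cos(2π(t + 0.5 − φ)/12), take the mean over the six months after divided by the mean over the three before, across all phases φ, with no programme effect:
- a = 10%: ratio from 0.87 to 1.16
- a = 20%: ratio from 0.75 to 1.35
- a = 30%: ratio from 0.66 to 1.59

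These ranges are for a single start month. Starts spread over the year would partly offset one another in a pooled estimate.

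**The case against.** The strongest reply is that the protocol never says period totals will be compared. Two indicators are recorded per month and a data officer collects them monthly, so the comparison can be read as one of monthly numbers, for which unchanged use gives 1.0. This stands: doubling follows from one reading of the wording and is not a certain result. It does not rescue the six-month follow-up indicator or an interpretation rule that carries no denominator. By contrast, the checklist analysis in the next section does specify change each month relative to baseline.

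The choice of model, offset and trend terms is commonly left to a statistical analysis plan, which is not at hand. That also stands, so their absence is not the point. The windows, the quantities and the interpretation rule are fixed in the protocol itself.

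Percentages of patients by diagnosis are not inflated by window length. That is correct.

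On season, a reader might infer that programme and season cannot be separated at all. The documents do not support that. Both dated waves are linked to August, but later start months are not given. The nurse interview period beginning in October 2014, described as following programme initiation, suggests that some starts fall elsewhere. The district clinic also supplies concurrent data. It is only a partial control: no seasonal use of it is described, and the programme works on referral pathways, so clinic volume may itself change.

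Finally, the process evaluation is described as an adjunct within a plausibility evaluation. That limits how elaborate the remedy should be, but not the need for a comparison on equal time.

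**Conclusion.** The point holds in a limited form. As worded, numbers from unequal windows are compared and any increase is read as uptake. If totals are used, unchanged use gives exactly 2.0, and a fall in monthly use of just under half passes the rule. That factor depends only on the stated windows. The probabilities in the table also depend on assumed monthly counts and on a test the protocol does not name, so they illustrate the risk and do not predict the result. It would go too far to conclude that Aim 1 is bound to succeed through window length alone, because monthly recording makes the error avoidable.

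Two weaknesses remain whichever reading is taken: the follow-up indicator has no equal-length pre-period, and season is uncontrolled within each centre. The size of any seasonal effect is unknown; the ranges above rest on assumed amplitudes. The wording should be corrected before the uptake data are analysed.

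**What to change.** 1. State that uptake is compared as rates per facility-month, for example with a Poisson or negative-binomial model of the monthly counts with centre effects.
2. Replace the rule on increased numbers with the resulting rate ratio and its 95% CI.
3. Define follow-up over the same length of time before and after implementation.
4. Where registers allow, extend the period before implementation so that the same calendar months are compared.

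Items 1 and 2 need only wording, since the monthly counts for total and new patients are already to be recorded. Items 3 and 4 may need extra extraction from the daily registers by the existing data officer. Step or slope terms at each centre's start date, and centres not yet started as concurrent comparators, would strengthen the analysis but are optional.

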*Analysis:* All participating patients will be included in the analysis. Patients who do not return for follow up will not be re-interviewed but will be included in final data analysis and we will examine baseline differences among those who do and do not complete follow-up interviews. Among patients who receive a score of  $> 2$  on the WHO DAS-II (indicating non-zero baseline disability) and a score of  $\geq 3$  on the GHQ-12 (indicating psychiatric caseness), we will calculate the percent of patients who experience clinically significant reductions in score (25% for the GHQ-12 and 20% for WHO-DAS-II Brief). Since there is currently no information on the percentage of individuals anticipated to achieve these score reductions within our population, we will assume this to be 50% (the most statistically conservative for sample size calculations – we expect this percentage to be greater which will increase our precisions). A sample size of 96 patients will allow us to estimate these proportions and 95% confidence intervals with precision of  $\pm 10$ . Assuming a drop-out rate of 20%, the minimum sample size for enrollment in the study will be 116. In order to stratify outcomes by characteristics such as age, gender, health center, diagnosis, and whether the patient is newly diagnosed or has previously been treated for a mental disorder, we will enroll as many patients are willing to participate (an estimate of 300 patients). We will use multivariable logistic regression to identify covariates associated with improved scores. Among individuals with low GHQ-12 and WHO-DAS-II Brief scores we will calculate within-person mean score change at eight weeks and four months. We will also calculate the percentage of patients who report improvements on the economic questionnaire and calculate mean score changes for individual responses.

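### The rule that reads a rise in visits as increased uptake does not use the hospital-clinic data collected alongside, so a change in place of care could be labelled uptake

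*Protocol*

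**What the plan says.** Aim 1 (Protocol, Study goals and objectives) is to "Assess changes in uptake of mental health care by assessing the quantity and quality of mental health diagnoses at Burera district health centers". The section Process Evaluation: routine quantitative program data supplies the method and the interpretation:

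- Window: "Routine program monitoring data will be collected for three months prior to and six months following the implementation of the MESH program".
- Rule: "An increase in the number of visits following MESH implementation will be interpreted as an increase in uptake of mental health services". No condition is attached.
- Hypothesis, in the Data analysis paragraph: "increase in the number of mental health diagnoses and follow-up visits at health centers post-MESH implementation, representing an increase in uptake of mental health services".
- Counts at each health center include "the number of new patients diagnosed with a mental disorder each month". Whether new means new to any mental health care or new to that facility is not defined.
- Hospital clinic: "These routine data will also be collected from the Butaro district hospital outpatient mental health clinic to assess district wide service use".
- Comparison: "We will also compare new and follow up data from health centers with routine data from the district mental health clinic".

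Age, gender and village are to be documented for each patient. Prior treatment is not among the items listed for these routine data. The Executive Summary and Program Research Evaluation name increased uptake among the things to be documented before national scale-up is considered.

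**The concern.** The rule and the hypothesis turn a health-center count into a statement about uptake. Two different things can raise that count. People who were not receiving mental health care may start, or visits that would have gone to the hospital clinic may take place at a health center instead. The rule gives both the same name.

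The second route is plausible from the protocol's own description. Background and Rationale describes specialist staff being placed at district hospitals first, with integration at health centers to follow. The MESH Mental Health Program section presents MESH MH as putting decentralization into practice and describes Butaro hospital as the referral center for seventeen health centers. Mentoring also covers referral pathways and coordination between services.

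Relocating care closer to home is a worthwhile result, but it is a different one from more care being taken up. Because uptake feeds the scale-up argument, the two should be kept apart.

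**Working it through.** The protocol gives no visit counts, effect size or power statement for Aim 1, so there is no figure to reproduce. The check is a count identity followed by an illustration. **All counts below are assumptions.**

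**Identity.** Let C and H be monthly visits before MESH at the health centers and at the hospital clinic, for the same villages. Let m be visits that move from hospital to health center one for one, and g be additional visits at the health centers.

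- Relative change at health centers = (m + g) / C
- Relative change at the hospital clinic = −m / H
- Relative change in the combined total = g / (C + H)

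The rule applied at health centers responds to m + g. Only the combined total isolates g.

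**Pure transfer (g = 0), C = 100, H = 200, total 300.**

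| m | Health centers | Hospital clinic | Combined |
|---|---|---|---|
| 25 | 125 (+25%) | 175 (−12.5%) | 300 (0%) |
| 50 | 150 (+50%) | 150 (−25%) | 300 (0%) |
| 100 | 200 (+100%) | 100 (−50%) | 300 (0%) |

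**Low prior use, C = 10, H = 30, total 40.** The health-center ratio is 1 + m/C. For m = 5, 10 and 20 it is 1.5, 2.0 and 3.0, while the combined total stays at 40. The distortion is largest where health-center use was low beforehand.

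**Same health-center rise, different meanings (C = 100, H = 200).** A rise from 100 to 150 fits each of these:

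- m = 50, g = 0: combined 300, change 0%.
- m = 25, g = 25: combined 325, change 25/300 = 8.3%.
- m = 0, g = 50: combined 350, change 50/300 = 16.7%.

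The rule returns increased uptake for all three. Using monthly rates for the three-month and six-month windows does not alter this.

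**Do the new-patient counts settle it?** Not as defined. If new means new to that facility's register, a hospital patient who starts attending a health center counts as new there, and nothing is subtracted at the hospital.

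**The case against.** The strongest reply is that the plan already covers this. Hospital-clinic data are collected for the stated purpose of assessing district-wide use, and a comparison with the health centers is promised. In a pure transfer that comparison would show the hospital falling as the centers rise, and how the two sources are combined could be left to an SAP that is not at hand. Much of this stands: a shift would be visible in planned data. What remains is that the protocol itself fixes how a rise will be read, and that reading is not conditional on the comparison.

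A second reply is that Aim 1 is set at health centers and that Study Design gives the process evaluation the job of showing whether MESH was implemented and its services provided. Health-center counts suit that purpose and should be kept. The difficulty lies in the label uptake, given its role in the scale-up case.

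A reader might infer that MESH moves existing hospital patients to health centers, so that a transfer would certainly be reported as more people reaching care. The documents do not support that. They nowhere say hospital patients are transferred, and the described treatment gap and training in case identification fit new case-finding equally well. A reader might also point to the outcome cohort, where results are to be stratified by "whether the patient is newly diagnosed or has previously been treated for a mental disorder". That shows a first visit need not be a first contact with care, but not where the earlier treatment took place. It could have been at the same health center.

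**Conclusion.** The point holds in a limited form. The protocol collects what is needed to tell a change in place of care from an increase in care, but its interpretation rule does not use it. To whatever extent visits shift from the hospital clinic, the rule as written counts that shift as uptake.

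The size cannot be stated from the documents. The illustration gives apparent health-center rises of 25% to 100% (or ratios of 1.5 to 3.0 where prior use is low) with no change in the combined total. It assumes one-for-one movement, no additional visits and invented baseline counts.

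The issue is confined to Aim 1. The process evaluation is an adjunct, and the primary outcomes (mental health status and daily functioning) are unaffected. It is worth correcting because the remedy is cheap and the uptake claim is meant to inform scale-up.

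**What to change.** In the routine program data section, including its Data analysis paragraph:

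1. Base the uptake conclusion on the pre/post change in monthly visits and new patients summed over the participating health centers and the hospital clinic. Restrict hospital patients to villages served by the MESH centers, using the village already recorded, and use the same calendar months.
2. Report the health-center count and its share of the combined total separately, as decentralization.
3. State that a health-center rise will not be called increased uptake unless the combined total also rises.
4. Say what new means. Let the visit total carry most weight, since a patient already known to the hospital may be entered as new at a health center, and one referred upward may be counted as new twice.
5. Use matching of new patients against the hospital register at most as a sensitivity analysis. The look-back is three months, diagnosis may itself change under MESH, and upward referrals could still be double-counted.

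Cost: mostly wording, with no new data items. Villages must be assigned to centers, and the protocol describes no such map. The reported gain may be smaller, and as a percentage it will look smaller even without any transfer because the denominator is larger (50/300 = 16.7% against 50/100 = 50%), so absolute changes should be shown as well.
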